### Endpoints

The primary endpoint is the MTD for which no dose-limiting toxicities (DLTs) occur. DLTs will be evaluated according to the Common Terminology Criteria for Adverse Events (CTCAE) version 5.0 (2017) continuously during the study until the first follow-up visit (4–6 weeks after surgery) for each patient and each dose level. Central nerve system necrosis (≥ grade 3), cerebrospinal fluid leakage (≥ grade 4), wound infection ((≥ grade 4), wound dehiscence (≥ grade 4), postoperative hemorrhage (≥ grade 4), cognitive disturbance (≥ grade 4), cerebral edema (≥ grade 4), headache (≥ grade 4), and seizure (≥ grade 4) are defined as DLTs.

Secondary endpoints are as follows:Central nerve system necrosis of CTCAE grade 1–3.Cerebrospinal fluid leakage of CTCAE grade 1–3.Wound infection of CTCAE grade 1–3.Wound dehiscence of CTCAE grade 1–3.Cerebral edema of CTCAE grade 1–3.Local control rates.OS and progression-free survival (PFS) at 12-month follow-up.Time interval between treatment initiation of neoadjuvant SRS and start of systemic chemotherapy.Health-related QoL evaluated using the EuroQoL questionnaire.Neurocognitive function assessed using the Minimal Mental State Examination (MMSE) test.Late toxicity of CTCAE grade 1–5.Immunological and molecular parameters [such as programmed death-ligand 1 (PD-L1) expression, Rapidly Accelerated Fibrosarcoma type B (BRAF) gene mutation, epidermal growth factor receptor (EGRF) mutation, and anaplastic lymphoma kinase [ALK] translocation on the resected specimen].

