The primary endpoint of this study is safety assessed from the start of radiotherapy until the first follow up after surgery (4–6 weeks after surgery). Based on experience from clinical practice, the number of patients lost to follow-up is expected to be very small. Patients who dropped out of the study between radiation treatment and first follow-up visit will be replaced by a new patient. For patients without a final examination after 1 year, the last valid examination will be used for the assessment of secondary endpoints. All secondary endpoints will be analyzed in an explorative manner using appropriate statistical methods: Mann–Whitney *U* Test (acute toxicity of CTCAE grade 1–3; late toxicity of CTCAE grade 1–5, immunological parameters, time interval between treatment initiation and start of systemic chemotherapy), Fisher’s exact test or Chi-square test (local control rates), log-rank test and Kaplan–Meier curves (OS and PFS at 12-month follow-up), Student *t* test (neurocognitive function), and scaled *t* test (health-related QoL) for independent patients.

The following parameters will be collected and taken into account in analyses applying regression models: age, Karnofsky performance score, extent of neurosurgical resection, recursive partitioning analysis (RPA)-classification.

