### Assessment of endpoints

The primary endpoint, MTD, will be assessed through extensive anamnesis and clinical neurological examination on the first postoperative day, the day of discharge from hospital, and the first follow-up visit at 4–6 weeks after surgery, with wound healing evaluated by an experienced neurosurgeon. This study will use the CTCAE version 5.0 for toxicity and adverse event reporting. Postoperative MRI (1–2 days after surgery) and the first follow-up MRI (4–6 weeks after surgery) will be evaluated by an experienced neuroradiologist, and the efficacy will be assessed according to the RECIST criteria [34].

For secondary endpoints, anamnesis and clinical neurological examination will be conducted as mentioned above. Disease progression is defined as radiological or neurological/clinical progression (whichever occurs first); PFS is considered the time interval between the date of treatment initiation and the date of disease progression or death, whichever occurs first. If neither event is observed, the patient will be censored at the date of the last follow-up examination. Neurocognitive function, QoL, and late toxicities will be evaluated at each follow-up visit every 3 months or at neurological deterioration (Table 2). Neuropathological work-up on the resected specimen will follow standard operating procedures at the Department of Pathology and will include immunologic as well as molecular parameters, such as PD-L1 expression, BRAF-gene mutation, EGFR mutation, and ALK translocation, where appropriate. Follow-up assessments (including MRI or CT) will be performed as described until disease progression (even after the termination of the study) in accordance with GCP and the treatment guidelines for patients with intracerebral metastases.

**Table 2 Tab2:** Time schedule of this study

Timepoint	Enrollment	Treatment				Follow-up (months)				Close-out (months)
	Day 0	Preoperative RT Day 1	Resection Days 2–7	Postoperative Days 1–2	Postoperative Days 3–5	1,5	3	6	9	12
Enrollment										
Eligibility screening	X									
Informed consent	X									
Study visit	X	X			X	X	X	X	X	X
Planning CT	Within 1–7 days after enrollment									
Planning MRI	Within 1–7 days after enrollment									
Interventions										
Neoadjuvant SRS		X								
Resection			X							
Assessments										
MRI	X			X		X	X	X	X	X
Clinical-neurological examination	X	X	X	X	X	X	X	X	X	X
Minimental state examination	X					X	X	X	X	X
Health-related QoL	X				X	X	X	X	X	X

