## Discussion

A study published by Asher et al. [21] evaluated the role of neoadjuvant SRS in 47 patients with 51 intracerebral metastasis lesions undergoing surgery at a median of 1 day (range 0–7 days) after neoadjuvant SRS. The median diameter of metastatic lesions was 3.0 cm (range 1.3–5.2 cm), and a dose reduction was applied with a median dose of 14.0 Gy (range 11.6–18.0 Gy) prescribed to the 80% isodose level. Local control rates were 97.8%, 85.6%, and 71.8% at 6, 12, and 24 months, respectively. Eight patients with local failure were re-operated and proved for recurrence without radiation necrosis. Local failure was more likely for lesions larger than 3.4 cm (*P* = 0.014). Due to the explorative character of their study, Asher et al. [21] were rather conservative in considering their dose prescription. Their doses were well below the dose thresholds that were established by the Radiation Therapy Oncology Group (RTOG) Trial 90-05, and it has to be kept in mind that those dose thresholds were set up for patients who had already received prior WBRT with a minimum dose of 30 Gy [35]. Patel et al. [22] conducted a trial, investigating neoadjuvant and postoperative SRS to the resection cavity in 180 patients with 189 intracerebral metastasis lesions being resected. In the neoadjuvant SRS cohort, the marginal dose was reduced by 20% (median dose, 14.5 Gy vs. 18.0 Gy) in analogy to that in the RTOG Trial 90-05 [35] with no extra margin added to the GTV (GTV = PTV) compared to the postoperative SRS cohort with an extra margin of 2 mm. GTV was similar, with 8.3 mL (range 0.89–46.8 mL) in the neoadjuvant SRS cohort versus 9.24 mL (range 0.68–54.60 mL) in the postoperative SRS cohort (*P* = 0.85). In the neoadjuvant cohort patients underwent intracerebral metastasis resection within 48 h after SRS. Outcomes were similar in regard of local recurrence, distant brain recurrence, and overall survival, but with significant lower rates of symptomatic radiation necrosis and leptomeningeal spread in the neoadjuvant SRS cohort than in the postoperative SRS cohort (4.9% vs. 16.4%, *P* = 0.01; 3.2% vs. 16.6%, *P* = 0.01) at 2 years, respectively [22]. In another work by Patel et al. [36], neoadjuvant SRS (66 patients with 71 lesions) was compared with postoperative WBRT (36 patients with 42 lesions); in analogy to that in the aforementioned study, the dose was reduced by 20% with no extra margin for PTV with surgery performed within 48 h after neoadjuvant SRS. Again, outcomes of the two cohorts were similar in terms of local recurrence, distant brain failure, and leptomeningeal disease recurrence. The rate of symptomatic radiation necrosis was higher in the neoadjuvant SRS cohort (5.6% vs. 0%), and the cavity size was significantly smaller (8.3 mL vs. 15.3 mL, *P* < 0.01) in this cohort. There was no analysis for QoL [36].

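### Late toxicity is tested by ranking grades at the last valid examination, which ignores time at risk and death and gives no necrosis rate at any time point

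*Protocol article*

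**What the plan says.** All points are from the protocol article.

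- **Endpoint.** The Endpoints section lists "Late toxicity of CTCAE grade 1–5" as a secondary endpoint and attaches no time window to it.
- **Test.** The Statistical analyses section calls the secondary analyses exploratory. It assigns the Mann–Whitney U test to a group of endpoints that includes "late toxicity of CTCAE grade 1–5, immunological parameters, time interval between treatment initiation and start of systemic chemotherapy". Kaplan–Meier curves and the log-rank test are named only for OS and PFS.
- **Missing 1-year visit.** The same section states: "For patients without a final examination after 1 year, the last valid examination will be used for the assessment of secondary endpoints".
- **Schedule.** Late toxicities are assessed every 3 months or at neurological deterioration (Assessment of endpoints). The last column of Table 2 is close-out at month 12.
- **After the study.** Follow-up assessments, including MRI or CT, "will be performed as described until disease progression (even after the termination of the study"). The article does not say whether findings from that period enter the late-toxicity endpoint.
- **Necrosis as a DLT.** CNS necrosis of grade 3 or higher is a DLT, assessed up to the first follow-up visit, 4–6 weeks after surgery (Endpoints; Statistical analyses).
- **Background figures.** The Discussion cites symptomatic necrosis, then leptomeningeal spread, for neoadjuvant against postoperative SRS as "4.9% vs. 16.4%, *P* = 0.01; 3.2% vs. 16.6%, *P* = 0.01) at 2 years, respectively". It also cites one necrosis at 4.6 months in another neoadjuvant series, and a further comparison of 5.6% with 0% without a time point.

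**The concern.** Late toxicity is an event that develops over time in patients who may die or be lost before month 12. A rank test on one grade per patient does not reflect this. A patient last seen at month 3 with no toxicity ranks level with one followed to month 12 with no toxicity. A group with more early deaths or losses can then look less toxic simply because it was watched for less time. Because the missing-data rule points to a single examination, a necrosis that has resolved by then may not count at all.

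The DLT window closes a few weeks after surgery, so necrosis that develops later can appear only in the late-toxicity endpoint. A rank test there gives the reader a P value and no answer to the obvious question: what proportion of patients had necrosis by a given time. Nor can its result be read beside any time-specific rate from the literature.

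**Working it through.** **1. The plan's own figures.** Minimum sample size 4 × [(3 × 3) + 3] = 48; maximum 4 × 6 × 3 = 72. Both reproduce. The article gives no target rate or precision for late toxicity, so these serve only as denominators.

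**2. What the stated rule does.** Take three hypothetical patients:

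| Patient | Course | Grade under the stated rule | Time-to-event record |
|---|---|---|---|
| A | Last examined at month 3, grade 0; then dies of another cause | 0 | Competing event at death |
| B | Grade 0 at every visit to month 12 | 0 | Censored at month 12 |
| C | Grade 2 necrosis at month 6, resolved by month 9, grade 0 at month 12 | 0 | Necrosis event at month 6 |

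All three are tied under the rule, although only B is known to be free of necrosis for a year. C is tied if the final examination supplies the grade. The article does not say that the worst grade is used, and the missing-data rule points to one examination.

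**3. Where necrosis can be seen.** Table 2 puts SRS on day 1 and resection on days 2–7, so surgery is at most 6 days after SRS. The DLT window then ends at most 6 + 42 = 48 days after SRS, about 1.6 months (48/30.4). The only onset time in the article is 4.6 months. This is a single case, but it lies outside the DLT window and inside the 12-month schedule.

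**4. Why a figure without a time point cannot be read beside the cited rate.** The article gives no necrosis rate by time, so I assume a constant hazard and take the cited 2-year rate of 4.9%.

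- Risk by month 12: 1 − (1 − 0.049)^0.5 = 0.0248, about 2.5%.
- Risk in months 12–24: 0.049 − 0.0248 = 0.0242.

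The same hazard therefore reads as 2.5% or 4.9% depending only on the time point.

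**5. Expected cases after month 12 in the whole trial.**

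| Assumption | n = 48 | n = 72 |
|---|---|---|
| Constant hazard, no attrition (n × 0.0242) | 1.16 | 1.74 |
| Constant hazard, 40% to 80% still at risk at month 12 | 0.46 to 0.93 | 0.70 to 1.39 |
| 20% to 65% of 2-year cases arise after month 12 (n × 0.049 × share) | 0.47 to 1.53 | 0.71 to 2.29 |

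For one dose level of six patients in one size cohort, the constant-hazard figure is 6 × 0.0242 = 0.15.

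**6. What level of detail the data can bear.** With no events among n patients and complete follow-up, the exact 95% upper limit is 1 − 0.025^(1/n).

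- One of the 4 × 3 = 12 dose-by-size cells: 71% (n = 3), 46% (n = 6).
- One dose level pooled over four cohorts, 12 to 24 patients if every cohort reaches it: 26% (n = 12), 14% (n = 24).
- Whole trial: 7.4% (n = 48), 5.0% (n = 72).

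Estimates are informative overall and marginal by dose level. Per cell, only counts are worth giving.

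**The case against.** The strongest reply is that late toxicity is an exploratory secondary endpoint in a phase I trial, that a 12-month close-out is a declared choice, and that the article condenses a fuller protocol. Most of this stands, and it rules out several stronger readings that a reader might infer:

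- **That the 2-year necrosis rate is the trial's benchmark.** It is Discussion background from one cited study. No objective, endpoint, sample size or analysis refers to it.
- **That necrosis after month 12 goes unreported.** The article is silent on this. The late-toxicity endpoint carries no time limit, and assessments continue after the study. Silence in a condensed article is not evidence of omission.
- **That a large, known share of necrosis falls after month 12.** Any such share rests on an assumed hazard. The single onset time given, 4.6 months, lends a constant hazard no support.
- **That the trial's doses exceed those of the neoadjuvant series it cites.** One cited series had a median of 18 Gy (range 12.6–24.4 Gy), against 12–22 Gy in Table 1.
- **That continued imaging would readily supply 24-month data.** It runs only until disease progression. Patients who progress leave it, and that loss may be informative.

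The reply does not rescue the analysis method. The rank test and the last-examination rule are stated in the article, not left to another document, and an exploratory label does not make them suit the endpoint. The article already uses time-to-event methods for OS and PFS.

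**Conclusion.** The point holds as a criticism of the stated analysis. Ranking late grades at the last valid examination disregards follow-up time and death, can lose resolved necrosis, and produces no rate. This follows from the text and needs no numerical assumption. The month-12 close-out is not an error, and a longer window is optional.

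The numerical stake is modest: about one to two necrosis cases after month 12 in the whole trial, and fewer after attrition. That rests on applying the cited 4.9% for symptomatic necrosis, from a series treated without an added margin, to this trial, and on a constant hazard. The gain is chiefly an interpretable 12-month necrosis figure from data the trial already plans to collect. Neither the MTD nor the recommended dose is affected, since both are set from DLTs up to 4–6 weeks after surgery.

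**What to change.** Replace the Mann–Whitney and last-examination analysis of late toxicity with:

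- the worst late-toxicity grade per patient over all late assessments, tabulated;
- the cumulative incidence of first CNS necrosis, for any grade and for grade 3 or higher, counted from SRS. Death is a competing event and other patients are censored at their last toxicity assessment. Report it at 12 months with confidence intervals.

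Pool across size cohorts, present results overall and by dose level I–III, and give only counts for each dose-by-size cell. Note that a pooled dose level covers different doses in Gy across the cohorts.

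State whether necrosis found in follow-up after study end counts towards the endpoint. If it does, a 24-month estimate may be added as descriptive, with a note that this follow-up ends at progression and that the loss may be informative.

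The Data collection section says that parameters of participants who discontinue are not collected and used. Censoring at the last assessment must be reconciled with that statement.

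Cost: revised analysis wording, an onset date for necrosis in the CRF, and a little more analysis. The 12-month results need no new visits, procedures or patients. The downside is wide intervals, above all by dose level and at 24 months.

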### Monitoring

An independent Data and Safety Monitoring Board (DSMB)/Data Monitoring Committee (DMC) will monitor the patient recruitment, reported adverse events, and data quality at least twice a year. Based on its review, the DSMB will provide the principal investigators (PIs) with recommendations regarding trial modification, continuation, or termination. The DSMB will be composed of independent experts in the field of radiation oncology. The mission of the DSMB will be to ensure the ethical conduct of the trial and to protect the safety interests of patients in this trial. Identified problems will be discussed with the PIs who will take appropriate measures. Relevant information (including relevant safety data) will be included in the study status reports, which serve as a basis of discussion for the study group meetings including the PI, study coordinator, and sub-investigators. The auditing will be conducted by the clinical site or by the DSMB and is independent from investigators and sponsors.

## Discussion

A study published by Asher et al. [21] evaluated the role of neoadjuvant SRS in 47 patients with 51 intracerebral metastasis lesions undergoing surgery at a median of 1 day (range 0–7 days) after neoadjuvant SRS. The median diameter of metastatic lesions was 3.0 cm (range 1.3–5.2 cm), and a dose reduction was applied with a median dose of 14.0 Gy (range 11.6–18.0 Gy) prescribed to the 80% isodose level. Local control rates were 97.8%, 85.6%, and 71.8% at 6, 12, and 24 months, respectively. Eight patients with local failure were re-operated and proved for recurrence without radiation necrosis. Local failure was more likely for lesions larger than 3.4 cm (*P* = 0.014). Due to the explorative character of their study, Asher et al. [21] were rather conservative in considering their dose prescription. Their doses were well below the dose thresholds that were established by the Radiation Therapy Oncology Group (RTOG) Trial 90-05, and it has to be kept in mind that those dose thresholds were set up for patients who had already received prior WBRT with a minimum dose of 30 Gy [35]. Patel et al. [22] conducted a trial, investigating neoadjuvant and postoperative SRS to the resection cavity in 180 patients with 189 intracerebral metastasis lesions being resected. In the neoadjuvant SRS cohort, the marginal dose was reduced by 20% (median dose, 14.5 Gy vs. 18.0 Gy) in analogy to that in the RTOG Trial 90-05 [35] with no extra margin added to the GTV (GTV = PTV) compared to the postoperative SRS cohort with an extra margin of 2 mm. GTV was similar, with 8.3 mL (range 0.89–46.8 mL) in the neoadjuvant SRS cohort versus 9.24 mL (range 0.68–54.60 mL) in the postoperative SRS cohort (*P* = 0.85). In the neoadjuvant cohort patients underwent intracerebral metastasis resection within 48 h after SRS. Outcomes were similar in regard of local recurrence, distant brain recurrence, and overall survival, but with significant lower rates of symptomatic radiation necrosis and leptomeningeal spread in the neoadjuvant SRS cohort than in the postoperative SRS cohort (4.9% vs. 16.4%, *P* = 0.01; 3.2% vs. 16.6%, *P* = 0.01) at 2 years, respectively [22]. In another work by Patel et al. [36], neoadjuvant SRS (66 patients with 71 lesions) was compared with postoperative WBRT (36 patients with 42 lesions); in analogy to that in the aforementioned study, the dose was reduced by 20% with no extra margin for PTV with surgery performed within 48 h after neoadjuvant SRS. Again, outcomes of the two cohorts were similar in terms of local recurrence, distant brain failure, and leptomeningeal disease recurrence. The rate of symptomatic radiation necrosis was higher in the neoadjuvant SRS cohort (5.6% vs. 0%), and the cavity size was significantly smaller (8.3 mL vs. 15.3 mL, *P* < 0.01) in this cohort. There was no analysis for QoL [36].

Vetlova et al. [23] analyzed a cohort of 19 patients with 22 metastases who underwent neoadjuvant SRS. The median tumor volume was 14.1 mL (range 3.0–57.1 mL), and the applied dose was 18 Gy in median (range 12.6–24.4 Gy), the surgery was carried out within 24–48 h after SRS. Two patients had local recurrence after 5.5 and 17.4 months of follow-up, and 1 had radiation necrosis at 4.6 months after treatment. Two patients died of disease progression.

The concept of neoadjuvant SRS for intracerebral metastases is characterized by a number of potential benefits compared with postoperative radiosurgery. Mostly, RT of the intact intracerebral metastases and surrounding normal tissues leads to a better definition of the target volume for RT, because postoperative changes, such as ischemia, scar tissue or blood-remnants, are missing. Therefore it is easier to spare normal tissue and consequently it can result in a higher safety of effective treatment of all tumor cells and subsequent lower damage to surrounding normal tissues. Additionally, the surgical tract does not exist before surgery; therefore, this area can be spared completely. Thereby, the rate of postoperative complications such as wound healing disorders and cerebrospinal fluid leaks could be reduced. After preoperative RT systemic chemotherapy or targeted therapy can be rapidly initiated after wound healing if needed in case of a high extracranial tumor burden. Contrary, systemic therapy is often delayed until postoperative RT is finished since some cancer therapies may not be applied during RT of the central nervous system or with high single doses.

This phase I study aims to find an optimal dose for neoadjuvant SRS for safe surgery and hence good outcome and local control. The trial incorporates a margin accounting for the microscopic spread and focuses on the dose escalation of this treatment strategy as well as QoL and neurocognitive function.

## Data Availability

The datasets collected and analyzed during the current study are available from the corresponding author on reasonable request.

## Abbreviations

SRS: stereotactic radiosurgery
FSRT: fractionated stereotactic radiosurgery
WBRT: whole-brain radiotherapy
MRI: magnetic resonance imaging
LINAC: linear accelerator
CTV: clinical target volume
ASTRO: American Society of Radiation Oncology
RT: radiation therapy
DEGRO: German Society of Radiation Oncology
CRF: Case Report Form
TMF: trial master file
ISF: Investigator Site File
ICH: International Council for Harmonisation
GCP: guideline on good clinical practice
MTD: maximum tolerated dose
DLT: dose limiting toxicity
CTCAE: Common Terminology Criteria for Adverse Events
MMSE: Minimal Mental State Examination
PD-L1: programmed death-ligand 1
ECOG: Eastern Cooperative Oncology Group
CT: computed tomography
GTV: gross tumor volume
CTV: clinical target volume
PTV: planning target volume
QUANTEC: quantitative analysis of normal tissue effects in the clinic
RPA: recursive partitioning analysis
PFS: progression-free survival
BRAF: B-Rapidly Accelerated Fibrosarcoma
EGFR: epidermal growth factor receptor
ALK: anaplastic lymphatic kinase
DSMB: Data and Safety Monitoring Board
DMC: monitoring committee
PI: principal investigator
RTOG: Radiation Therapy Oncology Group
